### Statistical analysis

In order to evaluate hypotheses of variables in contingency tables, the Chi-square or Fisher's Exact Tests will be used as appropriate. In order to test differences in continuous variables measured on at least interval scale between two independent groups the Student’s t-test for uncorrelated means will be used. The non-parametrical Mann–Whitney test will be used to test ordinal data. Regression analysis will be used to evaluate the dependency between variables and the Pearson correlation coefficient will be used in order to test independence between variables. In addition to that descriptive statistics will be used to characterize the data; means and 95% confidence intervals will be used for parametric data, medians and interquartile ranges for non-parametric data, and number (proportions) for categorical data. In case of multiple groups comparison. ANOVA, Kruskal–Wallis, and Chi-squared tests will be used respectively, along with post hoc analysis.

Protocol deviations will be recorded transparently. However, data from the different groups will be compared based on the'intention to treat'principle. An intention to treat (ITT) analysis means that all patients, regardless of treatment change, loss to follow-up or drop-out, remain in the analysis of the group to which they were randomized.

Statistical expertise will perform the statistical analysis.

Patient reported outcome measures consisting of ordinal scales for the different indices, will be compared using the Mann–Whitney test.

Data on total time on sick leave as well as the diagnosis used for sick leave will be collected.

Data on analgesic and antibiotic use will be collected from hospital files. Since different opioids may be used, conversion to morphine equivalents may be done. Data on other analgesics will be collected. Data on costs for the prescribed pharmaceuticals will be collected. Total amount of collected opioids (continuous data consisting of morphine equivalents) will be compared with the Student’s t-test or the Mann–Whitney test, depending on distribution.

Adverse events will be collected during the follow-up and classified as minor or major [30]. Data will be analyzed as dichotomous variables with Chi-square or Fisher tests.

Data on costs on the individual level will be collected. These consists of costs for the inpatient and outpatient visits (including surgery, radiographs, navigation), analgesic and antibiotic treatments, cost for sick leave. Working status at baseline and follow-ups will be queried.

Quality-adjusted life years (QALYs) will be calculated for each group (as measured by EQ-5D-5L). Combining cost and QALY yields incremental cost-effectiveness ratio (ICER) of the surgical intervention as compared to non-surgical care. To quantify the uncertainty around estimates, bootstrapping will be used. This allows the creation of the cost-effectiveness plane (a chart showing differences in outcomes and costs on each axis).

This ICER will then be compared to commonly used estimates of ICERs of other interventions (mainly surgeries and pharmaceutical interventions). Given the uncertainty around the official thresholds of willingness to pay for healthcare interventions, a cost-effectiveness acceptability curve will be drawn, showing the likelihood of the surgical intervention of being cost-effective given different levels of willingness to pay.

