### Inclusion criteria

• Written informed consent.

• Age 12 years and older.

• Spinal deformity surgery.

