#### Secondary outcomes related to implant density

Pedicle screw placement density comparison. The study aims for 100% pedicle screw density. Hooks may be placed as rescue or if screw placement fails.Final implant density compared to planned 100% pedicle screw density.Pedicle screw density.Hook density.Morphometric measurement for regression analysis.Pedicle diameters are measured on preop CT.Deformity correction rate.Cobb angle improvement.

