
### Study follow-up

Study visits are shown in Table 1. Patients will be assessed before the surgery, during the surgery and during the inpatient stay, as well as postoperatively at 3 months, 1 year, and through the Swespine registry at 2, 5, and 10 years. There will be no additional visits for the patients involved in the study compared to the clinical routine.

**Table 1 Tab1:** Study activities

	Visit 1: Screening Initial visit	Visit 2: Inpatient stay/surgery	Visits 3 + : 3 months +
Informed consent	X		
Demography	X		
Inclusion/exclusion criteria	X		
Randomization		X	
Outcome assessments	X	X	X*

^*^Outcomes assessed at regular clinical follow-ups; complications, standing spine radiographs. SRS-22r, EOSQ-24, ODI, EQ-5D-5L questionnaires collected as per Swespine routine on web or paper (preop, 1, 2, 5 and 10 years postoperatively)

Standard preoperative investigations include a low-dose computer tomography (CT), a whole spine standing radiograph and magnetic resonance imaging (MRI) of the spine. In case of navigation an intraoperative CBCT is performed. An intraoperative CBCT verification of implant positions is always performed in all cases of navigation and free hand procedures. In the immediate postoperative period, a low-dose CT is performed, as part of routine assessment. A whole spine standing radiograph is performed at 3 months and at 1 and 2 years. Curve size, type of scoliosis and other radiological parameters will be registered.

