### Sample size calculation

#### Sample size for primary objective

Based on our own and studies from others we estimate that accuracy at 1 st attempt in any of the navigated groups is p_nav_ = 91% and accuracy in the free hand group is p_control_ 84% [14, 28]. Consequently, a one-sided test can be used. With a power of 80%, alpha = 0.05, a sample size of 301 screws is obtained using sample size calculation for chi-squared test with continuity correction with equal group sizes. With a possible loss of data of 10% we aim for 332 screws in each group (rounded up to the closest integer).

With a mean of 15 screws inserted in each patient [29], about 22 patients are needed in each group. A forward calculation demonstrates that for these sample sizes, and with the same accuracy as described above, a p-value of 0.006 will be returned.

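### The primary accuracy comparison rests on an unadjusted screw-level chi-squared test; the baseline factors already collected and the stratification factor are not tied to it

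*Protocol article*

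**What the plan says.** - **Endpoint.** Under Primary outcomes, the endpoint is the number of screws graded 0 or 1 on the intraoperative verification scan, divided by the number of screws placed.
- **Sample size.** Under Sample size for primary objective, "we estimate that accuracy at 1 st attempt in any of the navigated groups is p_nav_ = 91" per cent and "accuracy in the free hand group is p_control_ 84" per cent. Then: "Consequently, a one-sided test can be used". "With a power of 80%, alpha = 0.05, a sample size of 301 screws is obtained" from a continuity-corrected chi-squared calculation with equal groups. Allowing for 10% loss gives 332 screws, or about 22 patients per group at 15 screws each.
- **Tests.** The Statistical analysis section starts "In order to evaluate hypotheses of variables in contingency tables" and names Chi-square or Fisher tests. It lists chi-squared again for comparisons of several groups. Regression is mentioned as a way to study dependency between variables, with no endpoint and no covariates named.
- **Population.** The Inclusion criteria admit spinal deformity surgery at "Age 12 years and older", with no upper age limit.
- **Baseline data.** Under Secondary outcomes related to implant density, "Pedicle diameters are measured on preop CT", in an item on morphometry intended for regression. Under Study follow-up, "Curve size, type of scoliosis and other radiological parameters will be registered".
- **Randomisation.** Operating theatre is the only stratification factor named. The two navigation systems stand in different theatres. No analysis mentions theatre.

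**The concern.** The protocol uses a crude two-by-two comparison of screws for its main question, while it collects variables that plausibly predict whether a screw breaches the pedicle. The Discussion calls small thoracic pedicles and scoliotic anatomy challenging, and it faults earlier studies for unequal case mix between arms. Randomisation here balances theatre only, so with about 22 patients per group pedicle size and curve severity are left to chance.

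Two things are at stake. If those factors are prognostic, an unadjusted analysis has a wider interval and less power than the same data could give. And randomisation is stratified by theatre, yet no stated analysis uses theatre.

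**Working it through.** **1. The plan's own figure.** Inputs: 0.84 and 0.91, one-sided 5%, 80% power. The mean proportion is 0.875.

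n = [1.645·√(2·0.875·0.125) + 0.842·√(0.84·0.16 + 0.91·0.09)]² / 0.07² = 275.

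With continuity correction: (n/4)·[1 + √(1 + 4/(n·0.07))]² = 303, against 301 stated. Then 301 × 1.10 = 331.1, rounded up to 332, and 332/15 = 22.1 patients. The figure reproduces closely. It contains no covariate and treats screws as independent.

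**2. What independence hides.** With 330 screws per group (22 × 15) and independent screws, one-sided power is 86%. With intra-patient correlation ρ the design effect is 1 + 14ρ. The protocol gives no ρ, so these values are assumed:

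- ρ = 0.05: 330/1.7 = 194 effective screws, power 67%.
- ρ = 0.10: 330/2.4 = 137.5 effective screws, power 54%.

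The fair comparison for adjustment is therefore a patient-clustered unadjusted analysis, not the chi-squared test.

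**3. Gain from adjustment (simulation, 22 patients × 15 screws per arm, 84% v 91%, one-sided 5%).** The protocol gives no prognostic strength. Assumed: observed covariates with a between-patient SD of 0.4, 0.6 or 0.8 logits and a within-patient SD of 0.7–0.8 logits, plus an unexplained patient SD of 0.4.

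| Between-patient SD explained | Unadjusted, clustered | Adjusted, clustered |
|---|---|---|
| 0.4 | 73% | 80% |
| 0.6 | 67% | 81% |
| 0.8 | 60% | 82% |
| covariates not prognostic | 76.5% | 76% |

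A second simulation used one patient-level and one screw-level covariate with equal effects and an adjusted linear model. Power went from 71% to 81% (0.5 logits per SD each, residual patient SD 0.3) and from 59% to 75% (0.8 each, residual SD 0.5). With no covariate effect it went from 87% to 85%. The variance of the adjusted difference, relative to the unadjusted, was 0.78, 0.67 and 1.02 in turn.

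I repeated these linear-model runs with the screw-level covariate dropped and only the patient-level one kept. In the prognostic scenarios power fell by only about 1 point, so most of the gain comes from between-patient differences.

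**4. Type I error of the chi-squared test.** Across the prognostic scenarios of both simulations, the naive screw-level test rejected a true null in about 8–15% of runs at a nominal one-sided 5%. The clustered analyses stayed near 5%.

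**5. Chance imbalance.** For one patient-level covariate, the standard error of the standardised difference is √(2/22) = 0.30. So P(|difference| > 0.25 SD) = 41% and P(> 0.5 SD) = 10%. Turned into accuracy under the assumptions of step 3, the SD of the resulting shift is about 1.6–3.0 points at 84% accuracy and about 1.1–2.0 points at 91%. A shift above 7 points occurs in at most 2% of trials.

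**6. Cost of a theatre term.** Each navigation system sits in one theatre. With theatre in the model, the comparison of the augmented-reality and infrared arms becomes (augmented reality − free hand in its theatre) − (infrared − free hand in its theatre). Assume 22 patients in each of the four cells, which fits the 44 navigated and 44 free-hand patients named under Sample size for secondary objectives. With equal variances, the variance goes from 2σ²/22 to 4σ²/22, so the standard error grows by √2 = 1.41.

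**The case against.** **The article is condensed and an analysis plan may name the model.** The quoted sentence is a general list of tests and does not name the primary endpoint, and regression is planned. This stands in part: a reader might infer that the plan rules out adjustment or reserves the covariates for secondary endpoints, and the text says neither. But the sample size ties the primary objective to chi-squared, the test list repeats it, and nothing ties the regression to that objective.

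**Imbalance is not bias.** Correct. A reader might infer that chance imbalance could match the planned 7-point effect. Step 5 shows this is rare, and a correctly clustered unadjusted test already allows for such imbalance in its error.

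**The prognostic claim goes beyond the text.** The Discussion says mainly that navigation helps most in neuromuscular scoliosis and in the thoracic spine. That is about where the technique effect is larger, and it does not establish pedicle diameter as the strongest predictor. This stands, so the gain can only be given as a range that includes none.

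**Adjustment is not the main repair.** This also stands. Ignored clustering threatens validity; adjustment adds precision. The power figures compare two clustered analyses, so they do not measure the loss from the chi-squared test itself.

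**Adjustment has traps.** The denominator is screws placed, and the Abstract expects navigation to allow screws in small pedicles. Diameter among placed screws may therefore depend on arm. The curve sentence follows the postoperative radiograph schedule and does not specify preoperative values. Many covariates with about 44 patients would strain robust standard errors. These points shape the fix but do not remove the need for it.

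**Conclusion.** The point holds as one of efficiency and specification. The only test the protocol links to the primary objective is unadjusted and at screw level. The collected pedicle diameters and the planned regression are not connected to it, and theatre is used in no stated analysis.

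Under assumed moderate to strong prognostic effects, clustered one-sided power rises from about 60–73% to about 80–82%; the second set of assumptions gives 59–71% rising to 75–81%. If the covariates carry no information, power is unchanged or falls by up to about 2 points. All of this assumes 22 patients and 15 screws per arm and the planned 84% v 91%. The covariate effects are assumptions, not protocol figures. The documents do not support a claim that the result would be biased, or that imbalance would typically rival the planned effect. The change is worth making before the data are analysed.

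**What to change.** Prespecify the primary analysis as a logistic model of screw accuracy with patient-level clustering, or a GEE with a small-sample correction. Terms:

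- arm and operating theatre;
- patient-level mean preoperative pedicle diameter over the planned levels, so that the covariate cannot depend on which screws were placed after randomisation;
- preoperative curve size, stated as preoperative;
- curve type only if coarsely grouped.

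Report the model-standardised difference in accuracy, so that the result remains a difference in proportions. Keep the crude proportions as descriptive. Use screw-level diameter in a sensitivity analysis.

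The cost is mainly wording. Preoperative CT and whole-spine radiographs are already routine, although diameters must be available for all planned levels, including those left without a screw. There are two downsides to state. A rule is needed for diameters that cannot be measured. And the contrast between the two navigation systems, estimated indirectly through free-hand patients once theatre is in the model, is less precise; report it with and without the theatre term.

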Most of the commercially available navigation systems are based on infrared cameras, using outside-in detection of reflective spheres on a dynamic reference frame fixed to the patient’s spine. Emerging video-based systems incorporating augmented reality (AR) for surgical navigation, along with intraoperative three-dimensional imaging, represent innovative computer-assisted navigation techniques [9–11]. These systems have demonstrated relatively high accuracy, safety, and effectiveness in previous studies reports on pedicle screw placement [4, 12, 13].

Nonetheless, as of now, the majority of data in this area is based on retrospective and a few prospectively collected series [12, 14, 15], while randomized controlled trials on spinal deformity are lacking. This is similar to the current situation of evidence on robotic pedicle screw placement, where the evidence from randomized studies comparing robotic guidance to navigation is scarce [6, 16, 17].

The aim of this trial will hence be to compare conventional and AR surgical navigation to free-hand technique based on three main study domains: implant placement accuracy, intraoperative radiation exposure and metrics, and operative time for navigation. Intraoperative adverse events will also be reported. Finally, since data on cost-effectiveness is crucial to ensure adequate allocation of healthcare resources, the cost-effectiveness of this technology will be assessed.

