### Study interventions and standard of care

#### Surgical treatment

All treatments involve surgical stabilization and fusion of the deformed spine. Additional surgical treatments for correction, such as osteotomies are performed as deemed by the treating surgeon.

All forms of treatment are available and used today at the Karolinska University hospital. The choice of supplier and brand of spine implants, as well as the use of intraoperative ARSN or IRSN are based on the preference of each surgeon. Neurophysiological monitoring is always performed as routine during spinal deformity surgery, with the exception of patients that are non-ambulatory. Motor evoked potential, sensory evoked potential and electromyography data will be collected to investigate any changes in neurophysiological parameters. Any deviations will be noted. Electromyography thresholds for all pedicle screws will be recorded.

Regardless of inclusion or randomization, patients will receive routine postoperative care including rehabilitation at the study center.

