#### Secondary outcomes related to surgical and postsurgical parameters

Patient reported outcome measures:oThe SRS-22r is a scoliosis specific questionnaire aiming to estimate quality of life in patients with scoliosis [24]. It contains 24 items divided into 5 domains covering function, pain, self-image, mental health, and satisfaction. An index value is calculated for each domain and a total index value is possible to calculate ranging from 1 (worst) to 5 (best). SRS-22r will be collected from Swespine.oEOSQ-24 is a proxy answered questionnaire and will be used in individuals up to the age of 15. It consists of 24 questions of daily function, pain, pulmonary function and mobility [25]. EOSQ-24 will be collected from Swespine.oOswestry Disability index (ODI). ODI is a back specific index measuring disability due to back pain [26]. It is the recommended instrument for studies concerning back pain. An index from 0–100 is calculated. An ODI of 0–20 indicate minimal disability, 21–40; moderate disability, 41–60; severe disability, 61–80; severely crippled, 81–100; bed-bound. ODI will be collected from Swespine.oEQ-5D 3 level is a generic quality of life instrument and consists of five areas reflecting mobility, self-care, usual activities, pain/discomfort and anxiety/depression [27]. Response alternatives range from no problems to extreme problems. An index can be calculated and depending on baseline value set used the index runs between approximately −0.5 (worst possible health) to 1.0 (best possible health). The EQ-5D-3L will be used for health economic analyses. The EQ-VAS is part of the EQ-5D and registers the patient’s self-rated health on a visual analogue scale (from 0 to 100; best). EQ-5D-3L will be collected from Swespine.Total procedure time as well as normalized to number of spinal levels from the upper to the lower instrumented vertebra.Intraoperative planning time (from start of planning in navigation software until last screw planned) (only when treated with ARSN or IRSN).Instrumentation time (total time for navigated/FH screw placement from first to last screw placement).Instrumentation time normalized to number of levels.Time for intraoperative verification imaging (CBCT and/or Fluoroscopy).Screw placement time (per screw, from owl to screw placed).Intraoperative blood loss.Intraoperative complications.Length of hospital stays.Administered doses of analgesia and types of analgesic medications required.Complications: at discharge, 30-, and 90-days.Readmissions and reasons for revision surgery: at 30-, 90-days, and 1-year.Costs per patient: at discharge, 30-, 90-days, and 1-year.

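### The ICER is defined for surgery versus non-surgical care, a contrast this all-surgical trial cannot estimate and which does not address its navigation question

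*Protocol article*

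**What the plan says.** The economic aim is given at the end of the Introduction. After setting out the comparison of conventional and AR navigation with free-hand technique, it says that "the cost-effectiveness of this technology will be assessed". Study outcomes and variables then sets the comparisons for primary and secondary outcomes: ARSN with free hand, IRSN with free hand, and ARSN with IRSN.

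The Statistical analysis section plans costs at the individual level, with navigation among the components, and QALYs for each group. The next step, however, "yields incremental cost-effectiveness ratio (ICER) of the surgical intervention as compared to non-surgical care". Bootstrapping and a cost-effectiveness plane follow, then an acceptability curve "showing the likelihood of the surgical intervention of being cost-effective given different levels of willingness to pay".

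Under Surgical treatment the protocol says: "All treatments involve surgical stabilization and fusion of the deformed spine".

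On the quality-of-life instrument, Secondary outcomes related to surgical and postsurgical parameters says: "The EQ-5D-3L will be used for health economic analyses". It adds that this version comes from Swespine. The footnote to Table 1 in Study follow-up has "SRS-22r, EOSQ-24, ODI, EQ-5D-5L questionnaires collected as per Swespine routine", and the QALYs in Statistical analysis are "as measured by EQ-5D-5L".

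**The concern.** An incremental ratio needs costs and QALYs on both sides of one contrast. The written contrast has surgery on one side and non-surgical care on the other, and the trial observes only the first. Read literally, the ICER cannot be estimated from trial data. Even with a comparator from elsewhere, it would describe the value of deformity surgery, not of navigating the screws.

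At stake is the pre-specification of the economic result. If the written contrast has to be set aside at analysis, someone must choose the replacement then, possibly with cost and EQ-5D data in hand. The choice between two EQ-5D versions raises the same problem on a smaller scale, because the QALY input is not fixed.

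**Working it through.** The documents give no ICER, QALY difference or willingness-to-pay figure, so there is no stated result to reproduce. The check sets the sections against each other.

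**Step 1: what the ratio needs.** For options A and B,

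ICER = (mean cost A − mean cost B) / (mean QALY A − mean QALY B).

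As written, A is surgery and B is non-surgical care.

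**Step 2: who could supply B.**

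- Arms (abstract; Fig. 1 text): ARSN, IRSN and free hand. Non-surgical arms: 0 of 3.
- Eligibility (Inclusion criteria; Subject enrollment): patients having spinal deformity surgery. Randomisation takes place during the operation, after exposure, so no randomised patient can be unoperated.
- Data sources (Table 2): Swespine, hospital files and case report form, dosimeters, and imaging or navigation equipment. Overview of study design describes Swespine as a quality registry for spine surgery. No non-surgical cohort, literature source or decision model is named.

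The number of comparator patients is 0, so mean cost B and mean QALY B are undefined. There is also nothing on that side to resample in the bootstrap.

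**Step 3: does the contrast match the question?**

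| Place | Contrast |
|---|---|
| Introduction (aim) | navigation against free hand |
| Study outcomes and variables | ARSN vs FH; IRSN vs FH; ARSN vs IRSN |
| Statistical analysis, ICER | surgery vs non-surgical care |
| Statistical analysis, acceptability curve | the surgical intervention, comparator not restated |
| Statistical analysis, plane | differences in outcomes and costs, contrast not restated |

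The ICER sentence names none of the three comparisons set for the outcomes. The curve repeats its subject, and the plane takes its contrast from it.

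**Step 4: could the intended contrast be estimated?** Yes. Costs per patient are a listed secondary outcome up to 1 year. EQ-5D is collected before surgery and at 1, 2, 5 and 10 years (Table 1 footnote). QALYs are planned per group. For ARSN against free hand, for example, all four means in Step 1 come from randomised patients. The same holds for the other two comparisons.

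**Step 5: EQ-5D version.** The outcomes section names 3L as the instrument, as the basis of the health economics and as what Swespine supplies. The Table 1 footnote names 5L as collected through Swespine, and Statistical analysis names 5L for QALYs. One registry and one analysis thus carry two versions. The outcomes section itself notes that the index range depends on the value set, so the version and value set both need to be fixed.

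**The case against.** The strongest reply is that the intent is plain. The aim is navigation, costs include navigation, QALYs are calculated for each group, and costs and EQ-5D are listed outcomes covered by the three stated comparisons. The surgery-versus-non-surgical wording appears explicitly in one sentence and is echoed in one more. The analysis is secondary, and the Limitations section already concedes that the sample is too small for full interpretation of secondary outcomes.

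Much of this stands. A reader might infer that the trial cannot answer the navigation question, or that its whole economic objective is lost. The documents do not support that: incremental costs and QALYs between arms can be computed from what is planned. A reader might also infer that an external non-randomised comparator will be brought in, but no section says so. The planned comparison of the ICER with published ratios for other interventions is a benchmark and supplies no costs or QALYs for non-surgical care. Nor does the 3L/5L conflict by itself prevent a between-arm comparison, since either version would serve if applied uniformly.

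What the reply does not remove is that the ICER is stated with the wrong comparator. This is not detail left to a fuller protocol or SAP: the article fixes a contrast, and it contradicts the design and the aim.

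**Conclusion.** The point holds for the ICER and for the plane and acceptability curve derived from it. As written, their contrast has no comparator patients in the trial and does not address navigation. It does not extend to the collection of costs and EQ-5D, to per-group costs and QALYs, or to the primary endpoint, randomisation or sample size.

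The EQ-5D conflict is a separate and smaller contradiction. How far QALYs would differ between the two versions cannot be worked out from the document, and no figure is claimed.

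The conclusion assumes that no non-surgical data source exists beyond those the article describes. If one does, the ICER might be estimable, but it would still not address the stated aim. The correction is worth making before the economic analysis begins, but as a secondary matter it does not threaten the trial's main result.

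**What to change.** In Statistical analysis, restate the ICER, the bootstrapped plane and the acceptability curve as incremental cost per QALY for the comparisons in Study outcomes and variables: ARSN versus free hand, IRSN versus free hand, and ARSN versus IRSN. Use the individual costs and per-group QALYs already planned. Remove the reference to non-surgical care, and make the navigation comparison the subject of the acceptability curve.

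Separately, confirm which EQ-5D version Swespine collects. Name that version in the outcomes section, the Table 1 footnote and Statistical analysis, and state one value set to be applied in all arms.

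The cost is wording and one check with the registry. No new data, visits or patients are needed. If the change is made after data have been seen, its date and reason should be reported.
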